## **E. Primary Safety**

The serious adverse events subdivided by perioperative, postoperative, and device related events will be presented descriptively. The number of subjects experiencing at least one event, the total number evaluated, the percentage, the exact 95% confidence interval on the percentage and total number of events will be presented

## **F. Secondary Effectiveness**

The cumulative area under the curve will be computed by the trapezoidal rule with the MAP as the amplitude and the duration as the base. The area under the curve computation involves summing across all time points the average amplitude for the beginning and ending time point times the unit of time between the two time points summed across all times when MAP was <65. This endpoint is correlated with the duration and a descriptive analysis of this endpoint will be presented with the mean, standard deviation, median, minimum and maximum across all patients with IOH of at least one-minute duration.

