## Analysis Summary

**Study Title:** Prospective, Single-Arm, Open-Label, Multicenter Study of Hypotension Prevention and Treatment in Patients Receiving Arterial Pressure Monitoring With Acumen™ Hypotension Prediction Index Feature Software (Clinical Protocol 2018-15)

**Primary Objective:** To determine whether the use of the Acumen™ HPI Feature Software to guide intraoperative hemodynamic management in non-cardiac surgery reduces the duration of intraoperative hypotension (defined as MAP < 65 mmHg for at least 1 minute) as compared with a historic retrospective control group.

**Primary Effectiveness Endpoint:** Duration (t [min]) reduction of intraoperative hypotension (defined as MAP < 65 mmHg for at least 1 minute) as compared with a historic retrospective control group.

**Primary Safety Endpoints:** Serious adverse events through 30 days as indicated below:

1. Serious Intraoperative and postoperative complications between each cohort;
2. Device-related serious adverse events.

**Secondary Effectiveness Endpoint:** The determination of total area under the curve (time and MAP) for IOH in each subject. This endpoint is correlated with the duration and a descriptive analysis of this endpoint will be presented with the mean, standard deviation, median, minimum and maximum.

**Secondary Safety Endpoint:** Percentages of subjects experiencing at least one of the following: postoperative episodes of non-fatal cardiac arrest, in-hospital death, stroke, AKI and MINS within 30 days of the procedure in the control and treated arms, respectively.

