### C. Secondary Effectiveness Endpoints

The secondary effectiveness endpoint is the determination total area under the curve of the time and MAP for all time periods for which MAP < 65 mmHG in each subject.

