#### 3. Area under threshold MAP < 65 mmHg

A measure highly correlated with duration of IOH is the area under the threshold of 65 mmHg. The area is computed by using the trapezoidal rule to estimate the area of pressure and time. The Total AUC is obtained using the formula below.

$$Total\ AUC = \sum_1^k \sum_1^l ((t_{ij} - t_{(i-1)j}) * (65 - (\frac{p_{ij} + p_{(i-1)j}}{2})))$$

where  $t_{ij}$  is the measurement time of the  $i$ th IOH increment of the  $j$ th IOH episode for the patient and  $p_{ij}$  is the mean pressure in mmHG for the  $i$ th IOH increment of the  $j$ th IOH episode. The episode for each patient begins,  $t_{0j}$ , with the first of two successive pressure measurements below MAP 65 mmHG and continues until the MAP raises to 65 mmHG or above. The trapezoidal rule sums the averages the decreases in pressure from 65 mmHG between two measurement times and multiplies that by the difference of the time increment between. Then the areas per episode are summed across the total number of episodes.

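### The secondary effectiveness area (SAP IX.F) multiplies MAP itself by time, so at equal duration deeper hypotension scores lower; it should use 65 minus MAP

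*SAP*

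**What the plan says.** The SAP lists one secondary effectiveness endpoint and describes it in three places.

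- **Analysis Summary:** "The determination of total area under the curve (time and MAP) for IOH in each subject".
- **Section V.C:** "total area under the curve of the time and MAP for all time periods for which MAP < 65 mmHG in each subject".
- **Section IX.F:** the area is "computed by the trapezoidal rule with the MAP as the amplitude and the duration as the base". The arithmetic is then spelled out as a sum, over the readings below 65, of each interval's average amplitude times its length. The summary statistics are taken "across all patients with IOH of at least one-minute duration".

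In all three, 65 mmHg selects the time points. It is never the line from which the amplitude is measured.

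A second area appears as an additional endpoint: item 2 in the Analysis Summary list and item 3 in section V.E. Its text reads "The Total AUC is obtained using the formula below", and the formula's amplitude is 65 minus the average of two neighbouring pressures. The explanation confirms this: "The trapezoidal rule sums the averages the decreases in pressure from 65 mmHG between two measurement times". Here an episode begins at the first of two successive readings below 65.

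Section VI makes the secondary endpoint descriptive, with nominal two-sided 95% confidence intervals shown if the primary test succeeds. Section IX.H gives the additional endpoints descriptive summaries.

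**The concern.** A summary of hypotension by area is useful because it combines how long pressure was low with how low it went. The SAP's Introduction itself notes that the association with organ injury was stronger at lower pressures, so depth should raise the score. With MAP as the amplitude, it lowers the score.

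A programmer who follows IX.F to the letter would produce a number driven mainly by minutes below 65, with an opposing contribution from depth. A reader would take it for hypotension burden. The naming adds to the risk: the secondary endpoint is called a total area under the curve, and the V.E formula is labelled Total AUC, yet the two rules give different quantities and the SAP never says how they relate.

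There is also a smaller matter of who is summarised. The Analysis Summary and V.C define the endpoint for each subject, while IX.F reports only subjects with at least one minute of hypotension.

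**Working it through.** The SAP gives no figure for this endpoint, so there is nothing to reproduce. The check applies the two written rules to the same traces. The traces are assumptions, because the SAP has no data on depth of MAP.

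**Rules.** With readings p at times t, over time below 65:

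- Rule A (IX.F): A = Σ (tᵢ − tᵢ₋₁) × (pᵢ + pᵢ₋₁)/2
- Rule B (V.E item 3): B = Σ (tᵢ − tᵢ₋₁) × [65 − (pᵢ + pᵢ₋₁)/2]

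**Identity.** Adding the two over the same intervals gives A + B = 65 × Σ (tᵢ − tᵢ₋₁) = 65T, so A = 65T − B. This holds for any trace. At fixed T, A falls by exactly as much as B rises.

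**Constant MAP for 10 minutes (65T = 650), in mmHg·min:**

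| MAP | A (IX.F) | B (V.E item 3) |
|---|---|---|
| 64 | 640 | 10 |
| 60 | 600 | 50 |
| 55 | 550 | 100 |
| 50 | 500 | 150 |
| 45 | 450 | 200 |
| 40 | 400 | 250 |

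From MAP 60 to MAP 45, A drops by 150/600 = 25%, while B rises by a factor of 200/50 = 4.

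**Varying MAP over 4 minutes (65T = 260).** Readings 64-62-60-62-64 give A = 63 + 61 + 61 + 63 = 248 and B = 260 − 248 = 12. Readings 64-52-40-52-64 give A = 58 + 46 + 46 + 58 = 208 and B = 260 − 208 = 52. The deeper trace again scores lower under A.

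**Unequal durations.** Longer hypotension raises A at a given pressure. Between MAP 64 and 40, each minute adds 64 to 40 to A, a ratio of 1.6, but 1 to 25 to B, a ratio of 25. A therefore mostly tracks duration. The ranking can still reverse when the deeper episode is the longer one: 10 minutes at 64 gives A = 640 and B = 10; 15 minutes at 40 gives A = 600 and B = 15 × 25 = 375.

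**Subjects without an episode.** If a fraction q has zero area, the mean among the rest is 1/(1 − q) times the mean over everyone. An assumed q of 10% gives 1/0.9 = 1.11, and 20% gives 1/0.8 = 1.25. The SAP states no value of q.

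**Episode rule.** The Analysis Summary and V.A define hypotension as MAP below 65 for at least one minute. V.E item 3 needs only two successive low readings. The Analysis Summary lists MAP at 20-second intervals, so two readings can span 20 seconds. V.C covers "for all time periods for which MAP < 65 mmHG in each subject", with no minimum length. Taking over the V.E formula unchanged would also bring in its episode rule.

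**The case against.** The strongest reply is that these are two different endpoints. The below-65 formula belongs to a separately listed additional endpoint, and the three descriptions of the secondary endpoint agree on MAP as the amplitude. A reader might infer that IX.F flatly contradicts V.E item 3. The SAP does not support that: the conflict is between near-identical names for different quantities. This stands, but it does not rescue IX.F, whose area still shrinks as pressure falls.

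A reader might also infer that the study would report no valid measure of burden. That is not so: the 65-minus-MAP area would still be summarised under IX.H. What is lost is its place as the secondary endpoint.

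A third reply is that the direction is wrong only at equal duration. That is correct, and the claim should be limited accordingly.

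On the subset, the restriction mirrors the control sample, which section V.A.1 describes as patients with at least one minute of hypotension. A reader might infer a treatment comparison biased by 11% or 25%. IX.F plans no comparison with controls, and those percentages rest on assumed proportions. What remains is that a summary limited to subjects with hypotension is not a summary of each subject.

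**Conclusion.** The rule in IX.F is wrong as written; this is more than missing detail. By the identity A = 65T − B, the only listed secondary effectiveness endpoint mostly measures duration and counts depth in the wrong direction at equal duration. The identity needs no assumption. The sizes shown (600 against 450, where the below-65 area gives 50 against 200) depend on illustrative pressures.

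The consequence is limited. The endpoint is descriptive, has no hypothesis test and no power calculation, and does not enter the primary test, the success criterion or the sample size. It would still mislead anyone who read the reported area as severity of hypotension.

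The restriction to subjects with at least one minute of hypotension is a lesser point. Its effect depends on a proportion that the SAP does not give.

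**What to change.** 1. In IX.F, make 65 minus MAP the amplitude, refer to the V.E item 3 formula, and state the unit as mmHg·min.
2. Bring the Analysis Summary and V.C into line, so that neither describes the area as one of time and MAP alone.
3. Apply the at-least-one-minute definition of hypotension consistently in V.C, V.E item 3 and IX.F, in place of the two-successive-readings start.
4. State that the additional endpoint is then the same quantity as the secondary endpoint, or remove the duplicate.
5. Summarise all analysed subjects, with an area of zero where there was no qualifying episode, and keep the at-least-one-minute subset as an extra row. Name the analysis set, since V.A assigns the full analysis set only to the primary endpoint.

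The cost is SAP wording and the matching program specification. The same MAP readings serve both rules, so no new data are needed.

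### The secondary effectiveness AUC uses MAP itself as the height, so it is mostly rescaled duration, misstates depth, and conflicts with the SAP's own area-under-threshold formula

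*SAP*

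**What the plan says.** Three places in the SAP describe the secondary effectiveness endpoint, and none of them subtracts pressure from 65 mmHg.

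- The Analysis Summary gives it as "The determination of total area under the curve (time and MAP) for IOH in each subject".
- Section V.C gives it as "total area under the curve of the time and MAP for all time periods for which MAP < 65 mmHG in each subject".
- Section IX.F, the analysis section, sets the computation: the area is "computed by the trapezoidal rule with the MAP as the amplitude and the duration as the base". It then spells out the trapezoid term as "the average amplitude for the beginning and ending time point times the unit of time between the two time points". Only time spent below 65 mmHg enters the total.

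Section V.E item 3 (item 2 in the Analysis Summary list of additional endpoints) defines a different area. It opens: "A measure highly correlated with duration of IOH is the area under the threshold of 65 mmHg". Its formula, labelled Total AUC, multiplies each time increment by 65 minus the average pressure, and its explanation reads "The trapezoidal rule sums the averages the decreases in pressure from 65 mmHG between two measurement times".

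IX.F does not refer to the V.E formula. The Analysis Summary lists the two areas as separate endpoints.

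**The concern.** An area measure is normally added to a duration endpoint because it also reflects how far pressure fell. With MAP as the height, depth enters with the wrong sign: of two episodes of equal length, the one with the lower pressure gets the smaller area. A programmer who follows IX.F literally will produce this quantity, because the section gives a complete algorithm of its own.

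This is the only secondary effectiveness endpoint. Under section VI it is presented with nominal 95% intervals once the primary test succeeds. A reader of the report would take it as the burden of hypotension, when it adds little to duration and misrepresents depth. Two different quantities would also appear in the same report under nearly the same name.

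**Working it through.** The SAP states no numerical AUC, so there is no figure to reproduce. The check compares the two formulas.

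**Inputs.** The IX.F and V.E item 3 formulas come from the SAP. So does the 20-second spacing, which the SAP lists for the advanced hemodynamic variables, MAP included. The constant-pressure episodes (MAP 40 to 64 mmHg; 5, 10 and 20 minutes) are illustrative assumptions.

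**Formulas.** Let dt be a time increment, p̄ the average MAP over it, and D the sum of the dt.

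- IX.F: A_raw = Σ dt × p̄
- V.E item 3: A_depth = Σ dt × (65 − p̄) = 65 × D − Σ dt × p̄

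Over the same intervals, therefore, **A_raw = 65 × D − A_depth**. The deficit enters the IX.F area with a negative sign.

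**Ten-minute episode (mmHg·min).**

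| MAP | IX.F: 10 × MAP | V.E item 3: 10 × (65 − MAP) |
|---|---|---|
| 64 | 640 | 10 |
| 60 | 600 | 50 |
| 55 | 550 | 100 |
| 50 | 500 | 150 |
| 45 | 450 | 200 |
| 40 | 400 | 250 |

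From MAP 60 to MAP 45, the IX.F area falls by 25% (450/600 = 0.75) while the deficit rises fourfold (200/50). The ordering is the same at 5 minutes (IX.F 320 down to 200; V.E 5 up to 125) and at 20 minutes (IX.F 1280 down to 800; V.E 20 up to 500).

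**Equal scores for unequal episodes.** Ten minutes at MAP 45 scores 450 under IX.F. An episode at MAP 64 reaches the same score in 450/64 ≈ 7.0 minutes. Under V.E item 3 the two score 200 and about 7.

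**Why it is mostly duration.** Across MAP 40 to 64 the IX.F height varies by a factor of 64/40 = 1.6. The V.E height varies from 1 to 25. Duration varies widely: section V.A.1 gives the control data a mean of 28.2 minutes and an SD of 42.5. Doubling an episode at MAP 60 from 10 to 20 minutes doubles the IX.F area from 600 to 1200, whatever the depth.

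**Episode rules.** V.E item 3 opens an episode only when two consecutive readings lie under 65 mmHg, dated from the earlier one. IX.F adds up all time below 65 mmHg and summarises patients who had at least one minute of IOH. The identity above assumes the same intervals, which the two sections as written do not guarantee.

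**The case against.** The strongest reply is that IX.F is loose prose for the V.E formula. The V.E label, Total AUC, echoes the wording of the Analysis Summary and V.C. Both areas use the trapezoidal rule, both are described as correlated with duration, and the depth form is the only one written as an equation. That may well be what was intended. But the SAP lists the two as separate endpoints, IX.F gives its own full algorithm, and nothing links the two sections. If the V.E formula was meant, one quantity is listed twice without saying so. Either reading needs a correction.

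The limits on impact do stand, and they rule out several stronger inferences.

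- **The endpoint runs backwards on severity in general.** It does not. The IX.F area still rises with duration; the reversal holds only at a given duration.
- **A device that shortened but deepened episodes would beat control on this endpoint.** IX.F plans no control comparison and no test of the area, only a descriptive summary of treated patients.
- **Information on depth is lost, or the result cannot be related to an area under threshold.** The depth area is still reported under V.E item 3, and the identity converts one into the other over the same intervals.
- **The additional endpoint must be deleted.** It need not be. Deletion could break agreement with the protocol, which is not at hand, and would not settle the episode rules.

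**Conclusion.** The point holds as an error of definition in a descriptive endpoint. As written, the secondary area is 65 × duration minus the depth-based area, so depth counts in the wrong direction at a given duration (600 against 450 mmHg·min where the deficits are 50 and 200). The SAP has two conflicting area computations under nearly one name, and the higher-ranked endpoint carries the one that misstates depth.

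The primary endpoint, its one-sided 0.025 test, the success criterion and the sample size are unaffected. The algebraic identity depends only on the two formulas applied to the same intervals. The worked figures depend on the assumed constant-pressure episodes and show direction and scale; they do not predict trial results.

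**What to change.** 1. In IX.F, make (65 minus MAP) the amplitude in place of MAP, and cite the V.E item 3 formula.
2. In V.C and the Analysis Summary, rename the endpoint as the area under the 65 mmHg threshold, in mmHg·min.
3. Use one episode rule in both IX.F and V.E item 3, and state how it fits the one-minute definition of IOH. If MAP is read every 20 seconds, two consecutive readings span only 20 seconds.
4. State that additional endpoint 2 of the Analysis Summary (V.E item 3) is the same quantity as the secondary endpoint, or how it differs. It can remain in the list.

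The cost is SAP wording, a one-line change to the area formula, and whatever programming the agreed episode rule needs. No new data are required. It should be settled before the data are analysed, so that the definition is not chosen with results in view.

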## **G. Secondary Safety**

The descriptive presentation will be given for the 30-day composite endpoint with any of the following events: postoperative non-fatal cardiac arrest, in-hospital death, stroke acute kidney injury, and myocardial injury in this non-cardiac surgery. This endpoint will be presented descriptively with the number of subjects experiencing one or more of the composite events, the total number evaluated, the percentage and the exact 95% confidence limits on the percentage. The number of subjects experiencing each element of the composite with the number of events will also be presented descriptively.

## **H. Additional Effectiveness Endpoint Analyses**

For each additional endpoint listed above the presentation will be descriptive. For continuous endpoints, the mean, standard deviation, number evaluated, median, minimum, and maximum will be presented. For categorical endpoints, the number with the property, the total number evaluated, the percentage, and the exact 95% confidence limit on the percentage will be provided.

## **X. Statistical Software**

The primary analyses will be done using SAS, Version 9.4 or later for Personal Computers. The Fisher's exact tests, exact 95% confidence limits, and other categorical data computations will be done with StatXact for windows (Version 8 or later). Some preliminary descriptive analyses and figures may be done with Minitab Version 17 or later.

